### Interim analyses {21b}

Not applicable. No interim analysis will be performed.

### Methods for additional analyses (e.g. subgroup analyses) {20b}

For sensitivity analysis, baseline differences between treatment arms are assessed with the independent Student’s *t* test or Wilcoxon rank sum test and if needed, multivariable analyses will be used to adjust for possible imbalances. Subgroup analysis will be performed for CABG and AVR surgery patients separately.

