### Trial design {8}

This is a randomized placebo-controlled double-blind multi-centre superiority trial with two parallel groups in which IVI is compared to a placebo. The patient allocation ratio is 1:1, stratified by centre and type of cardiac surgery.

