### Sample size {14}

In the previously conducted AGE cohort (ClinicalTrials.gov Identifier NCT02535728) studying a similar patient population, the mean WHODAS 2.0 score for CABG and AVR patients after 3 months was 12% points with a standard deviation (SD) of 15% points. For an expected effect size, a mean difference in WHODAS 2.0 score of 5% points or more between the treatment and placebo groups was chosen. This difference in WHODAS 2.0 score is consistent with a clinically relevant change in disability [18]. We based our sample size estimate on the most conservative (largest) standard deviation, which was 15% points. To detect a mean difference in WHODAS 2.0 score of 5% points at 90 days using a two-tailed unpaired *T*-test with a two-sided significance level of 5% and a power of 80% with equal allocation to two arms would require 142 patients per treatment group. Taking into account a loss to follow-up margin of 10%, we aim to include a total cohort of 310 patients. Calculations were performed using R version 3.6.1—© 2019–07-05, R, Inc., for Windows.

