## Statistical methods

### Statistical methods for primary and secondary outcomes {20a}

Data will be analysed using R statistics (version 3.5.1—© 2018–07-02, R, Inc., for Windows). Descriptive statistics will be calculated for all study parameters. Continuous data will be described as mean (+ standard deviation) and median (+ interquartile range) for normally and non-normally distributed data, respectively. Categorical variables will be described as numbers and percentages. The effect of IVI therapy on the primary and secondary endpoints will be analysed with ANCOVA and logistic regression analysis. All analyses are performed according to the intention-to-treat principle. Two-sided *P* values of 0.05 or less will be considered statistically significant.

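### CABG and AVR patients are to be analysed separately with no stated treatment-by-surgery interaction, which does not test whether the effect of iron differs by operation

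*Protocol article*

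**What the plan says.** The section on additional analyses {20b} gives the whole subgroup plan in one sentence: "Subgroup analysis will be performed for CABG and AVR surgery patients separately". It names no outcome, model, interaction term, test of heterogeneity or rule of interpretation for the subgroups, and none appears elsewhere in the article.

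The only significance rule is in the section on statistical methods {20a}: two-sided P "values of 0.05 or less will be considered statistically significant". It makes no exception for subgroups. The ANCOVA for the primary outcome adjusts for baseline haemoglobin and baseline WHODAS-12. Surgery type is not among its stated terms.

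Surgery type is, however, a randomisation factor. Trial design {8} states: "The patient allocation ratio is 1:1, stratified by centre and type of cardiac surgery". The trial is sized for the whole cohort: "To detect a mean difference in WHODAS 2.0 score of 5% points at 90 days" with "a power of 80% with equal allocation to two arms", the plan "would require 142 patients per treatment group".

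**The concern.** A reader of a subgroup analysis by operation wants to know whether iron works differently after CABG than after AVR. Two within-operation P values do not answer that. One can fall below 0.05 and the other above it when the true effects are identical, simply because each subgroup is smaller than the trial that was powered.

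At stake is the interpretation of a secondary analysis. The Discussion raises possible routine use of intravenous iron in anaemic patients after cardiac surgery. A result that appears to favour one operation could steer that use without the data supporting a difference.

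**Working it through.** **Inputs from Sample size {14}:** difference 5 points; SD 15 ("the most conservative (largest) standard deviation, which was 15% points"); "a two-sided significance level of 5"%; power 80%; 142 per arm, so 284 evaluable. Allocation is 1:1.

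**Assumptions:** the CABG:AVR split is not stated, so 50/50 to 80/20 is used. The subgroup outcome is taken to be the 90-day WHODAS score.

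**The plan's own figure.** n per arm = 2 × (1.960 + 0.842)² × 15² / 5² = 141.3, rounded up to 142. This reproduces the stated number. An exact t calculation gives 143, with 79.9% power at 142.

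**Power within a subgroup of n patients.** SE = 15 × √(4/n), and power ≈ Φ(5/SE − 1.96). For a 50/50 split, n = 142 (71 per arm):
- SE = 15 × √(4/142) = 2.52
- power = Φ(1.986 − 1.96) = 0.510

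**Chance that exactly one subgroup is significant.** The subgroups contain different patients, so with powers a and b the chance is a(1 − b) + b(1 − a). At 50/50 this is 2 × 0.51 × 0.49 = 0.50.

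| Assumed split | Power, larger / smaller | Exactly one significant | Both significant |
|---|---|---|---|
| 50/50 | 51% / 51% | 50% | 26% |
| 60/40 | 59% / 43% | 51% | 25% |
| 70/30 | 65% / 34% | 55% | 22% |
| 80/20 | 71% / 24% | 61% | 17% |

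**No effect in either operation.** 2 × 0.05 × 0.95 = 9.5%, at any split.

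**Sensitivity.**
- With 310 less 10% = 279 evaluable, the chance of exactly one significant subgroup changes by less than 1 point.
- If baseline adjustment lowers the SD to 15 × √(1 − 0.5²) ≈ 13 (assumed correlation 0.5), that chance is 47% to 54% for splits of 50/50 to 70/30.
- Among simulated trials with a true 5-point effect in both operations and a significant overall result, exactly one subgroup is significant in 57% (50/50) to 71% (80/20).

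**The interaction test.** When the true effects are equal, a two-sided 5% test signals a difference in 5% of trials at any split. Its SE is 15 × √(4/n₁ + 4/n₂):
- 50/50: SE = 15 × √(4/142 + 4/142) = 3.56. Power for a true 5-point difference between operations is 29%, and 80% power needs 2.80 × 3.56 ≈ 10.0 points.
- 80/20: SE = 15 × √(4/227.2 + 4/56.8) = 4.45. Power is 20%, and 80% power needs 2.80 × 4.45 ≈ 12.5 points.

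**The case against.** The strongest reply is that this is one sentence in an article that condenses a longer protocol. Reporting effects by operation is compatible with also testing an interaction, and an analysis plan that is not shown may do so. The 0.05 rule stands in the section on primary and secondary outcomes, and nothing commits the investigators to conclusions from subgroup P values. There is also only one subgroup factor, named in advance and used in randomisation, so this is not a search through many subgroups.

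Much of that stands, and it limits what can be said. Three stronger readings are tempting but unsupported:

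- A reader might infer that the plan rejects an interaction test or will claim effect modification from subgroup P values. The article does neither. An exactly-one-significant result becomes a false claim only if someone interprets it that way.
- A reader might infer that a benefit in one operation only is likely to appear by chance whatever the truth. That holds only if something near the full 5-point effect is real in both operations. With no effect in either, the figure is 9.5%.
- A reader might infer that each subgroup holds about half the sample. The split is not given, hence the range.

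The reply does not remove the point. The article does more than stay silent: it states how the subgroups will be analysed, and the stated analysis leaves the subgroup question untested.

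**Conclusion.** The point holds in this limited form. Separate analyses are the only subgroup method stated, and they do not test whether the effect differs by operation.

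The 50% to 61% for exactly one significant subgroup rests on a true 5-point effect in both operations, SD 15, 284 evaluable patients, each subgroup being judged at 0.05, and the assumed splits. The comparison is with a 5% false-positive rate for a single interaction test. The remedy controls false claims of a difference but will seldom detect a real one of moderate size. This is a matter of secondary analysis and its reporting; the primary comparison and the sample size are untouched.

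**What to change.** Replace the subgroup sentence, or specify in the analysis plan before unblinding, as follows:

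- Fit one model in all patients: the planned ANCOVA plus surgery type and treatment-by-surgery type. The primary ANCOVA itself stays as planned.
- Report the interaction estimate with its 95% CI and P value.
- Show the effect within each operation with a 95% CI, as description only, and draw no conclusion from within-subgroup P values.
- Label the analysis exploratory. State that the interaction test has low power, so a non-significant result is not evidence that the effects are equal.

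The cost is wording. Surgery type is a randomisation stratum and is therefore known for every randomised patient, so no extra data or patients are needed. The downside to accept is that the interaction interval will be wide: with an SE of 3.56 to 4.45, its half-width is 1.96 × SE, or about 7.0 to 8.7 points.

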### Methods in analysis to handle protocol non-adherence and any statistical methods to handle missing data {20c}

We intend to test superiority using an intention-to-treat analysis. Thus, all randomized participants, regardless of protocol adherence, as randomized to treatment allocation will be included in the analysis. Missing data will be reduced to a minimum, as described above. However, in case of missing data, these will be compared between the two groups, and imputed using multiple imputations.

### Plans to give access to the full protocol, participant-level data and statistical code {31c}

The datasets used and/or analysed during the current study can be made available by the corresponding author upon reasonable request and in agreement with the research collaboration and data transfer guidelines of the participating hospitals.

## Oversight and monitoring

### Composition of the coordinating centre and trial steering committee {5d}

This is a multicentre study, initiated in two hospitals.

For day-to-day support, the following roles are assigned:The coordinating investigator is responsible for trial registration, the coordination of study visits and the communication between participating hospitals and annual safety reports.The principal investigators in the participating hospitals supervise the trial and the medical responsibility of the patients. They are responsible for data management (organizing data capture, safeguarding quality and data). Furthermore, the principal investigators are responsible for patients’ recruitment, the attainment of informed consent and follow-up.

The study team meets twice a month. There is no Trial Steering Committee or stakeholder and public involvement group.

### Composition of the data monitoring committee, its role and reporting structure {21a}

A data safety monitoring board (DSMB) has not been appointed for this study since the risk classification for this study is low. The study population (elderly cardiac surgery patients) is considered a high-risk population. The intervention, however, is considered a low-risk intervention because of the following reasons:First, the study drug is approved by the EMA in the EU in 2009 and is already a common treatment for IDA.Second, the study drug will be used within its approved indication in the study, and subsequently, the risks associated with the treatment are considered low. Third, the patient’s vital signs are continuously monitored during and after treatment (at the ICU). Lastly, even though there is a small risk for acute severe hypersensitivity reactions (an anaphylactic reaction is rare (incidence is < 0.1%)), the EMA concluded that the benefit-risk balance of IVI treatment is favourable as the benefits outweigh the risks in the treatment of iron deficiency when used under their current indications.

### Adverse event reporting and harms {22}

Adverse events (AEs) are defined as any undesirable experience occurring to a subject during the study, whether or not considered related to the investigational product. All AEs reported spontaneously by the subject or observed by the investigator or staff will be recorded. All AEs will be evaluated for severity, seriousness and relatedness to the investigational product. A serious adverse event (SAE) is any untoward medical occurrence or effect that:Results in deathIs life-threatening (at the time of the event)Requires hospitalization or prolongation of existing inpatient’s hospitalizationResults in persistent or significant disability or incapacityIs a congenital anomaly or birth defectAny other important medical event that did not result in any of the outcomes listed above due to medical or surgical intervention but could have been based upon appropriate judgement by the investigator

The investigator will report all SAEs to the sponsor without undue delay after obtaining knowledge of the events, except for the SAEs which are common after cardiac surgery and do not require immediate reporting, such as cardiogenic shock (> 1 h after infusion), (supra)ventricular arrhythmia, atrioventricular block, congestive heart failure, acute kidney injury, pneumonia, pulmonary embolus, stroke, sepsis, wound infection, urinary tract infection, delirium, reoperation and ICU readmission (from general ward). The SAEs described above will be recorded in an overview list (line-listing) that will be submitted once every half year to the Medical Ethical Committee. This line-listing provides an overview of all SAEs, accompanied by a brief report highlighting the main points of concern. All other SAEs will be reported to the CCMO following the CCMO guidelines.

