### Intervention description {11a}

The patient will undergo surgery according to standard practice. Postoperatively, patients will be admitted to the ICU (standard care). On the first postoperative morning, the iron status will be assessed from a routine blood sample in patients with uncomplicated surgery who meet the ICU discharge criteria. Patients with IDA will be randomly allocated to either the treatment group or the placebo group. Patients randomized to the treatment arm will be administered a single dose of ferric derisomaltose (Monofer®) 100 mg/mL solution for infusion in 60 min. The method of administration and dosage of the investigational medication are standard treatment. The ferric derisomaltose dose will be calculated for each patient depending on ideal body weight (20 mg/kg) and diluted in 250 mL NaCl 0.9%. The maximum ferric derisomaltose dose is 2000 mg. The placebo group will receive 250 mL NaCl 0.9% w/v in 60 min. The study medication will be administered before ICU discharge by a trained nurse. Vital signs of the patient will be monitored during administration of the study medication and for 30 min afterwards. The study medication will be administered through a central venous catheter which is placed after induction of anaesthesia before the start of surgery (standard care). No additional venous access is required to administer the study medication. Both the infusion bag and the infusion line are light-protected (Codan®). Participation in the trial will not delay ICU discharge.

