### Criteria for discontinuing or modifying allocated interventions {11b}

Patients can leave the study at any time for any reason without any consequences. The patient data that have been collected up to that moment will be included in the analysis. Acute severe hypersensitivity reactions may occur with parenteral iron preparations. They usually occur within the first few minutes of administration and are generally characterized by the sudden onset of respiratory difficulty and/or cardiovascular collapse. In the case of signs/symptoms of acute hypersensitivity reactions or anaphylactic shock (frequency is rare: incidence is less than 0.1%), the intervention will be discontinued and the patient will be excluded from the study. An excluded patient will be replaced by a new patient. Hypersensitivity reactions and anaphylactic shock will be treated according to standard protocol. In addition, a Fishbane reaction may occur in patients treated with IVI. A Fishbane reaction is characterized by flushing of the face, acute chest and/or back pain and tightness in the chest, which is sometimes accompanied by dyspnoea. This may mimic the early symptoms of an anaphylactic reaction. However, they disappear shortly after administration is discontinued. Approximately 15 min after the symptoms have disappeared, the infusion will be restarted with a 50% lower infusion rate. A Fishbane reaction typically does not reoccur if IVI administration is restarted at a lower infusion rate and is therefore not necessarily a reason to exclude the patient from the study.

In accordance to Sect. 10, subsection 4, of the Dutch Medical Research with Human Subjects Law (WMO (Wet medisch-wetenschappelijk onderzoek met mensen)), the sponsor (St. Antonius Hospital) should suspend the study if there are sufficient grounds that continuation of the study will jeopardize subject health or safety. However, ferric derisomaltose is an IV therapy approved by the EMA. The EMA concluded that the benefit-risk balance of intravenous iron is favourable in the treatment of iron deficiency when used under their current indications. In this study, ferric derisomaltose will be used within its approved indication, and subsequently, the risks associated with the treatment are considered low.

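### The exemption from prompt SAE reporting is set by event type: it ignores relatedness, and only cardiogenic shock carries a time limit relative to the infusion

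*Protocol article*

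**What the plan says.** The default in section {22} (Adverse event reporting and harms) is strict: "The investigator will report all SAEs to the sponsor without undue delay after obtaining knowledge of the events". An exemption follows at once: "except for the SAEs which are common after cardiac surgery and do not require immediate reporting, such as cardiogenic shock (> 1 h after infusion"). The list goes on with "supra)ventricular arrhythmia, atrioventricular block, congestive heart failure, acute kidney injury, pneumonia, pulmonary embolus, stroke, sepsis, wound infection, urinary tract infection, delirium", and ends with reoperation and with ICU readmission from the general ward.

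Exempted events take another route. They "will be recorded in an overview list (line-listing) that will be submitted once every half year to the Medical Ethical Committee". For the rest, "All other SAEs will be reported to the CCMO following the CCMO guidelines".

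The same section requires each adverse event to be assessed for severity, seriousness and relatedness, and it names death as one criterion for seriousness. Section {11b} puts the decision to halt the trial on the sponsor, which "should suspend the study if there are sufficient grounds that continuation of the study will jeopardize subject health or safety". Section {17b} allows a code break for a SUSAR. On oversight, section {21a} states: "A data safety monitoring board (DSMB) has not been appointed for this study since the risk classification for this study is low". Section {5d} reports no steering committee, and section {21b} plans no interim analysis.

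**The concern.** Exempting expected postoperative events from expedited reporting is normal in cardiac surgery. It is safe when the exempt events are ones that cannot plausibly inform a judgement about the drug. Here the exemption depends on what the event is called. It does not depend on whether the investigator thinks the drug caused it and, with one exception, it does not depend on whether the event happened while the drug was running in.

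Section {11b} describes the recognised acute hazard as a sudden respiratory or cardiovascular event, usually within minutes of starting the infusion. Several exempt terms are acute cardiovascular events. If one occurs during the infusion and is filed under its exempt name, the party responsible for suspending the trial has no stated entitlement to hear of it promptly.

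**Working it through.** No design figure depends on this point, so the check compares the sections with one another.

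**1. What defines the exemption.** Counting the events named in section {22} gives 14: cardiogenic shock, (supra)ventricular arrhythmia, AV block, congestive heart failure, acute kidney injury, pneumonia, pulmonary embolus, stroke, sepsis, wound infection, urinary tract infection, delirium, reoperation and ICU readmission. They are introduced as examples, so the set is not closed.

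**2. Timing.** One of the 14 (cardiogenic shock) has an explicit limit relative to the infusion. One more (ICU readmission) has an implicit one: it must be from the ward, and section {11a} has study drug given before ICU discharge. That leaves 14 − 2 = 12 with no timing condition, including arrhythmia, AV block, heart failure and stroke. Taken literally, shock at minute 5 of the infusion is not exempt, but a serious arrhythmia or AV block at minute 5 is. The limit on shock shows that the authors regarded closeness to the infusion as relevant.

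**3. Where the hour starts.** Section {11a} sets a 60-minute infusion. Counted from the start, the exempt period for shock opens at minute 60, as an uninterrupted infusion finishes. Counted from the end, it opens at minute 60 + 60 = 120. The two readings differ by a full hour.

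**4. Relatedness.** It is assessed for every adverse event in section {22}, but no sentence there uses the result to decide the reporting route.

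**5. Fatal outcome.** Death is a criterion for seriousness. It is not on the exempt list, and the list has no exception for it. A fatal stroke could be filed as a listed event (stroke) or as one of the other SAEs. Two sites could choose differently and both be following the text.

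**6. SUSARs.** Section {17b} recognises them and section {23} has their reporting checked. Neither says that SUSAR handling takes precedence over the exemption.

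**7. Who sees the data.**

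| Safeguard | Section | Described as reviewing accumulating safety data? |
|---|---|---|
| Vital-sign monitoring during and after infusion | {11a}, {21a} | No, individual patient |
| Study team, meeting twice a month | {5d} | Not stated |
| Independent monitor of source data and (S)AE/SUSAR reporting | {23} | No, and no visit frequency given |
| DSMB | {21a} | None appointed |
| Steering committee | {5d} | None |
| Interim analysis | {21b} | None |

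**The case against.** The strongest reply is that the named hazard is already covered. Hypersensitivity and anaphylaxis are not on the exempt list, so a serious case goes by the ordinary route. The listed term nearest to cardiovascular collapse is cardiogenic shock, the one with a time limit. The exemption is also worded for events that do not need immediate reporting, which leaves some room for judgement. SUSARs are recognised, and the full protocol, which is not shown, may settle their precedence.

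Much of this is fair. It narrows the problem to events that present as a listed term and not as an evident hypersensitivity reaction. It does not remove the problem. The article states the exemption as an operating rule, down to a bracketed time limit, and that rule gives an investigator who judges a listed event related no instruction to report it promptly.

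Some stronger readings are tempting but unsupported:

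- **That nobody is watching.** Bedside monitoring, a study team meeting twice a month and an independent monitor all exist. What is missing is a body described as reviewing accumulating safety data.
- **That the sponsor waits half a year.** The half-yearly interval is for the listing to the ethics committee. For the sponsor, the article lifts the prompt-reporting duty and sets no interval in its place.
- **That the number of patients randomised between two listings measures the harm.** Such a count needs the planned recruitment pace, while the Trial status section reports only thirty included. It would also describe exposure, not harm.
- **That the 30-minute observation period in section {11a} contradicts the 1-hour limit.** One is a bedside monitoring period and the other a reporting cut-off. They need not match.
- **That deaths are expressly exempt.** They are not; the text is ambiguous.

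**Conclusion.** The point holds as a defect in a stated rule. The exemption is set by event type through an open list, takes no account of relatedness, and applies an explicit infusion-time limit to 1 of 14 named events, with the start of that hour undefined. A listed event that occurs during the infusion or is judged related therefore carries no duty of prompt report to the sponsor, and it reaches the ethics committee in a listing sent every half year. How the exemption applies to fatal listed events and to SUSARs is unresolved.

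This rests on reading the article's text as the rule that sites follow. If the full protocol already gives precedence to SUSARs and deaths, those two ambiguities disappear. The timing and relatedness gaps remain unless it also qualifies the list. The point concerns safety oversight only and leaves the sample size, the randomisation and the efficacy analysis untouched. It should be corrected because the trial relies on the sponsor's decision to suspend, with no DSMB or steering committee.

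**What to change.** Amend section {22} as follows:

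- Replace the open list with a closed one.
- Limit the exemption to listed events that are non-fatal, judged unrelated to study medication, and outside a single peri-infusion reporting window. The sponsor should define that window, apply it to every listed term, and state whether it runs from the start or the end of the infusion.
- State that all other SAEs go to the sponsor without undue delay, and that SUSAR handling takes precedence over the exemption.
- Reconcile the result with the sponsor's suspension duty in {11b} and the code-break procedure in {17b}.

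This keeps the sensible core of the exemption and changes reporting only. The cost is a wording amendment, a briefing at the sites, and some additional immediate reports for fatal, related or peri-infusion events. A by-arm version of the half-yearly listing is not needed and is better avoided: it would produce repeated comparative data with no rule for reviewing them, and add a risk to blinding.
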